**Figure 1 F1:**
[figure not shown]
**Steps in identifying potentially eligible patients**.

In Step 2, patients who have an upcoming clinic appointment receive a recruitment letter, followed by a screening telephone call. Based on responses given during the screening telephone call, patients who meet any of the exclusion criteria listed Step 2 of Figure 1 are excluded. Patients passing Step 2 are scheduled for an in-person screening visit with a research assistant (RA). Spouses are also required to attend; in most cases, spouses have been able to come at the same time as patients. This may not be true in a younger population that is more likely to be employed and caring for young children.

In Step 3, self-reported data and laboratory results obtained during the screening visit, combined with medical record data, are used to count patients' risk factors and calculate their Framingham risk scores (see Figure 1, Step 3). This information is used to determine patients' risk categories, as defined in Table 1, and their individual LDL-C goals based on the risk categories. Patients with above-goal LDL-C are eligible for enrollment. Eligible couples are randomized, as a pair, to the intervention or control arm. The randomization is stratified on patient race (White and non-White) and risk category (collapsed from three categories to two – high and medium/low – due to the low prevalence of the low-risk category). This will allow us to test for differential effects of the intervention on different race and risk groups, which will inform future interventions.

The screening visit also serves as the baseline visit for eligible patients. At this visit, patients and spouses provide written informed consent, complete baseline measures, and receive printed educational materials. After the visit, the research nurse who delivers the CouPLES intervention places a telephone call to inform patients of their laboratory results, eligibility, and when eligible, randomization assignment. During this telephone call as well as the intervention telephone calls preceding follow-up assessments, the nurse instructs couples not to reveal their study assignment to the RA so that the RA will be blinded for outcome assessments. Each couple receives $40 for each of the three visits.

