#### Control variables

Demographic variables (age, sex, race, education, financial stress, employment status) and clinical variables (cholesterol medication use, frequency of cholesterol testing, alcohol and tobacco use, antihypertensive medication use, family history of CHD) are assessed at via self-report. Health literacy is assessed with the Short Test of Functional Health Literacy in Adults (S-TOFHLA).[15] Comorbidities are assessed with a self-report checklist.[16]

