### Sample size and statistical power

The primary hypothesis is:

(H1) An 11-month, telephone-based patient-spouse intervention will result in a greater reduction in LDL-C as compared to printed education materials.

In our sample size calculations, we assume no change for patients who receive only printed education materials and a 7% reduction in LDL-C (based on a 2-month pilot study using the same intervention materials) for intervention patients from baseline to 11 months. Based on a standard deviation adjusted to account for correlation between repeated measurements of the outcome, and using an independent samples t-test with a 0.05 two-sided significance level and 80% power, a sample size of 100 patients per group is required to detect a 9.4 point (7%) difference in change of LDL-C values between the intervention and control groups. Because we assume an approximate dropout rate of 20%, we will recruit approximately 125 couples per arm.

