### Primary analyses

The unit of analysis is the patient. Because LDL-C, a continuous variable, is assessed at baseline, 6 months, and 11 months, we will use a linear mixed-effects model (LMM).[23] Fixed effects in the model will include intervention group, time, and the interaction between these two variables. This will enable us to determine the effects of the intervention at both 6 and 11 months. Patient-level random effects will be included in the model to account for correlations between patients' repeated measures over time. Primary analyses will be conducted as intent-to-treat, and sensitivity analyses will examine the implications of the intent-to-treat assumption.

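### Randomization is stratified on race and risk category, but the stated primary LDL-C model contains neither factor; the race and risk comparisons that stratification is meant to serve should be labelled exploratory

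*Protocol article*

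**What the plan says.** Under Patient population and recruitment, the protocol article states: "The randomization is stratified on patient race (White and non-White) and risk category". Risk category is reduced to high versus medium/low. The reason given is: "This will allow us to test for differential effects of the intervention on different race and risk groups".

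Under Primary analyses, the LDL-C model is a linear mixed model with patient-level random effects. Its fixed part is given as: "Fixed effects in the model will include intervention group, time, and the interaction between these two variables". Neither race nor risk category is named. Secondary analyses adds hypotheses on medication adherence, exercise and calories, but no comparison of effect by race or risk.

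Under Sample size and statistical power, the only target is the overall difference between arms: "a sample size of 100 patients per group is required to detect a 9.4 point (7%) difference in change of LDL-C values", "using an independent samples t-test with a 0.05 two-sided significance level and 80% power". With 20% dropout assumed, about 125 couples per arm are recruited. No power is stated for any subgroup comparison, and the expected stratum shares are not given.

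**The concern.** Stratified randomization forces the arms to be alike on race and risk category. An analysis that leaves those factors out does not take credit for that balance. Variation between strata stays in the error term, so the standard error of the treatment effect is larger than the design warrants. Risk category deserves particular attention because Table 1 ties it to the LDL-C level required for entry (100, 130 or 160 mg/dL) and the screening visit doubles as baseline. Strata selected at different cut-offs could regress to the mean by different amounts, and a patient random intercept does not absorb a difference in change over time.

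The second issue is the purpose given for stratifying. Balance within strata makes a comparison of effects between strata fair, but it does not make it powerful. The article says the results will inform future interventions. With low power, a null interaction could be read as proof of equal benefit, and a chance difference as grounds for targeting one group.

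**Working it through.** **1. The plan's own figure.** Inputs from Sample size and statistical power: difference 9.4 mg/dL, two-sided alpha 0.05, power 80%, 100 per group, 20% dropout. The SD is described but not given ("Based on a standard deviation adjusted to account for correlation between repeated measurements of the outcome"), so it has to be solved for:

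SD = 9.4 / [√(2/100) × (1.960 + 0.842)] = 23.7 mg/dL, or 23.6 with the t distribution.

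Because the SD is solved from the 100 per group, this does not check that figure independently. The recruitment figure does reproduce: 100 / (1 − 0.20) = 125 per arm.

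**2. Does omitting the strata harm the primary test?** A difference between strata that is constant over time largely cancels from the group-by-time contrast, because the patient random effects absorb it. Only a stratum-by-time difference matters.

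*Type I error.* This was simulated as a two-arm comparison of change under the null: 200 patients, two strata of 100, arms exactly balanced within strata, 20,000 replicates. The stratum effect on change is in within-stratum SD units.

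| Stratum effect | Rejection, factor omitted | Rejection, factor included |
|---|---|---|
| 0.3 SD | 0.050 | 0.051 |
| 0.5 SD | 0.043 | 0.048 |
| 0.8 SD | 0.036 | 0.049 |

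Omitting the factor makes the test conservative; it does not inflate the error rate.

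*Precision.* If the factor explains a fraction f of the variance of change, the standard error shrinks by the factor √(1 − f), and power becomes Φ(2.802/√(1 − f) − 1.960).

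- f = 1%: SE falls 0.5%, power 80.4%.
- f = 2%: SE falls 1.0%, power 80.8%.

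The 1-2% for risk category comes from applying the Table 1 entry thresholds to an assumed clinic LDL-C mean of 115 mg/dL, SD 33 and between-visit correlation 0.6-0.8. None of those inputs is in the documents. For range, at a 50:50 split f = 0.25g²/(1 + 0.25g²) for a stratum effect of g SD:

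- g = 0.3: f = 2.2%, power 80.9%.
- g = 0.5: f = 5.9%, power 82.3%.
- g = 0.8: f = 13.8%, power 85.5%.

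**3. Power for a difference in effect between strata.** With share p of patients in one stratum and n evaluable per arm:

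SE(interaction) = 23.6 × √[2/(np) + 2/(n(1 − p))]

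Power for difference D = Φ(D/SE − 1.960) + Φ(−D/SE − 1.960), and the difference detectable with 80% power is 2.802 × SE. The back-solved SD cancels when D is expressed relative to 9.4. The splits are assumptions.

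| n per arm | Split | SE | Power at D = 9.4 | 80% detectable |
|---|---|---|---|---|
| 100 | 50:50 | 6.68 | 29% | 18.7 mg/dL |
| 100 | 80:20 | 8.35 | 20% | 23.4 mg/dL |
| 125 | 50:50 | 5.97 | 35% | 16.7 mg/dL |
| 125 | 80:20 | 7.47 | 24% | 20.9 mg/dL |

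With 100 per arm, the detectable difference is 2.0 to 2.5 times the whole target effect (18.7/9.4 and 23.4/9.4). At 50:50, a difference of 14.1 mg/dL (1.5 × 9.4) has 56% power and one of 18.8 mg/dL (2 × 9.4) has 80%. The latter would mean, for example, 18.8 in one half and nothing in the other, averaging 9.4.

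**The case against.** The strongest reply is that this is an article, that will include need not be an exhaustive list, and that subgroup terms are commonly left to the analysis plan. The section on control variables, listing "clinical variables (cholesterol medication use, frequency of cholesterol testing" among others, even hints that some adjustment is intended. This stands in part. The absence of a full subgroup specification is not a fault in itself, and adjusting for baseline drug use is a choice, since it is not a stratification factor. It does not remove the main point. The article does state the fixed part of its primary model, and that statement omits both factors used to randomize.

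A second reply is that the gain is negligible. On the assumed inputs for risk alone that is fair: less than one percentage point of power. It limits the weight of the point, but the change is also nearly free. What race would add is unknown.

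Three stronger readings are tempting and are not supported:

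- **The primary test is invalid.** It is not. Omission is conservative, and the different entry thresholds do not bias the group-by-time contrast merely by shifting baseline levels.
- **The strata are needed for the dropout assumptions to hold.** Nothing in the article says dropout depends on race or risk, and the mixed model already conditions on observed LDL-C.
- **The trial promises subgroup tests that always have under 30% power.** The article claims no power for them, and the figure is conditional. It holds for a difference no larger than 9.4 mg/dL with 200 evaluable patients. Analysing all 250, or a larger difference, can exceed it.

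**Conclusion.** The point holds as a modest improvement to the analysis. The stated primary model does not match the stratified design. The consequence is mild conservatism and a precision loss that is likely small, about 1-2% of the variance of change for risk category on inputs that the documents do not supply. The validity of the primary comparison is not in question.

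The secondary point also holds in conditional form. The sample size does not support confirmatory conclusions about differences in effect by race or risk. For a difference equal to the target effect, power is roughly 20-29% with 200 evaluable patients and 24-35% with all 250, over assumed splits from 80:20 to 50:50. More uneven splits would lower it: at 90:10 with 200 evaluable patients it is about 13%.

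**What to change.** Add race stratum and risk stratum, each with a time interaction, to the fixed effects of the primary LDL-C model. With time as a three-level factor this is 2 × (1 + 2) = 6 further parameters, which is little against about 200 evaluable patients. Both variables are already recorded in order to randomize. Adjusting for baseline lipid-lowering drug use is optional.

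In a separate model, estimate how the arm difference in LDL-C change at 11 months varies by race and by risk category, as group-by-factor interaction contrasts with confidence intervals. Label these exploratory. Where the article explains why randomization is stratified, add that the trial was not sized for these comparisons and give the detectable difference (about 18.7-23.4 mg/dL with 200 evaluable patients), recalculated at the actual stratum shares. The cost is a few lines of wording, with no change to sample size, visits or data collection.

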### Secondary analyses

The secondary hypotheses are that patients who receive the intervention will have significantly greater medication adherence and exercise, and consume fewer calories, compared to patients who only receive printed education materials. Because these outcomes are continuous and are assessed at three time points for each patient, we will use LMMs. We are also interested in changes in self-efficacy, spousal support, and patient-physician communication. We will examine whether changes in these process measures are responsible for changes in LDL-C at both 6 and 11 months using currently accepted methods.[24,25]

### Economic evaluation

The period of analysis will be the 11-month intervention period. The base-case cost analysis will be conducted from the VA's perspective. We will estimate the average annual cost of the intervention per patient as well as the cost of resource utilization, focusing on primary care visits and cholesterol medications. Additionally, if the intervention is more effective than printed education materials, we will assess the incremental cost-effectiveness of the intervention. For the cost-effectiveness analysis, we will use percent reduction in LDL-C as the effectiveness measure.

## Discussion

Recommended therapies for LDL-C reduction are only effective if patients are adherent.[26,27] Unfortunately, patient adherence to CHD prevention treatment is sub-optimal, resulting in LDL-C levels above guideline-recommended goals. Increasing the support provided to patients is likely to improve their adherence to treatment recommendations. In the CouPLES trial, we are assessing the effectiveness of teaching patients and spouses strategies to help increase patient adherence, which in turn should lower LDL-C levels.

The CouPLES intervention is novel in a number of respects. First, to our knowledge, this is the first patient-spouse intervention that addresses all major components of the lipid-lowering regimen. Second, rather than receiving topical modules in a prescribed order, patients can decide which modules they would like to receive and how often. They can choose one topic for the entire duration of the study or choose any combination of topics. Third, we use multiple modes to deliver the information, including printed educational materials, telephone calls, and reinforcement by spouses. This is important because patients typically receive information in one format (usually verbally) in a single clinical encounter and are likely to misunderstand or forget it. Fourth, the nurse teaches spouses how to provide emotional and instrumental support rather than just suggesting that they should be involved. Fifth, the nurse tailors suggestions according to whether spouses intend or do not intend to make the same lifestyle changes as patients. Finally, the intervention is delivered by telephone, which has several advantages over face-to-face strategies, including lower cost and wider reach.[28,29] Telephone interventions allow a nurse to follow a much larger panel than would be possible with in-person interventions. For this reason, we will assess the cost effectiveness of the intervention to help determine the resources that would be necessary to implement it.

## Conclusion

CHD is associated with significant healthcare costs, with nearly $130 billion in direct and indirect costs in 2003.[1] The expected increase in prevalence of CHD over the next several decades will result in an increased burden for many health care systems. Despite the known risk of elevated LDL-C, patients are not adhering to the behaviors necessary to achieve optimal LDL-C levels. Given that the latest recommendations have even lower goals for LDL-C,[30] more effective interventions are needed. If the CouPLES intervention proves effective and low-cost, it could help reduce future healthcare costs associated with the long-term effects of elevated LDL-C levels.

## Abbreviations

CHAMPS: Community for Healthy Activities Model Program for Seniors; CHD: coronary heart disease; CouPLES: couples partnering for lipid enhancing strategies; FFQ: food frequency questionnaire; LDL-C: low-density lipoprotein cholesterol; LMM: linear mixed model; mg/dL: milligrams per deciliter; RA: research assistant; S-TOHFLA: Short Test of Functional Health Literacy in Adults; VA: Veterans Affairs; VAMC: Veterans Affairs Medical Center.
